### Procedure for unblinding if needed {17b}

N/A, as assessors, who are the only blinded members of the study team, are always accompanied by a training supervisor, who knows the participants and their group allocation. Hence, in case any situation during a measurement session would require knowledge of group allocation, the training supervisor can handle it and the assessor does not need to be unblinded.

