### Trial design {8}

This study is a randomised, controlled trial (RCT) with two parallel arms, investigating the superiority of a concept-guided, personalised, motor-cognitive exergame training added to usual care over usual care alone. The trial employs a single-blinded approach, with outcome assessors being unaware of group assignments. The randomisation is performed with a 1:1 ratio using stratification by sex (female or male [73]) and cognitive impairment (MoCA ≥ 24 or MoCA < 24 [74]).

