## Assignment of interventions: blinding

### Who will be blinded {17a}

Outcome assessors are blinded to group allocation. They cannot access the randomisation tool in REDCap and are not involved in intervention procedures. To blind the data analyst, a de-identified dataset will be used for analysis, which will not contain unique identifiers such as the study ID.

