## Data collection and management

### Plans for assessment and collection of outcomes {18a}

All outcome variables are gathered in an eCRF (see the ‘Data management’ section). All study-team members gathering data receive specific training for the relevant study procedures. Primary and secondary outcomes are collected at baseline (T0), post-intervention (T1), and follow-up (T2) measurements. The MoCA (primary outcome) is executed on paper following the instructions of the providers (mocacognition.com [93]), and the data is transferred into the eCRF. All assessors obtain a MoCA certificate (mocacognition.com) for trained execution of the test before performing the assessment in the study. The SIS 3.0 is collected via an online questionnaire filled out by the participants electronically in the eCRF or, in case not able to do so, on paper and transferred to the eCRF by the investigators. Secondary computer-based cognitive assessments are conducted within the Vienna Test System (VTS, Schuhfried GmbH, Mödling, Austria), a valid and reliable software for neuropsychological testing. All assessments include written instructions and practice sets and are only started if the participant received clarifying responses on any questions regarding the test functionality. The tests are performed on a touch-screen computer, using either one button on the keyboard or the touch screen to answer the stimuli. All cognitive outcome variables are obtained from the VTS result sheets and transferred into the eCRF. Outcome variables for the TUG and TUG-Cog are collected using a stopwatch and by noting correct answers on paper and directly entered into the eCRF. For the TUG, TUG-Cog, and the 10MWT, practice trials are performed before the actual assessment to ensure clarity of the procedure. Outcome variables of the gait assessments are gathered using the Gait Up system (Gait Up SA, Lausanne, Switzerland) with Physilog® sensors (wearable standalone movement inertial sensors, 50 × 37 × 9.2 mm, 19 g). The Gait Up system provides quantitative, objective, and valid assessment of gait movement [143] presented on output sheets, from where the data are transferred into the eCRF. The first and last two gait cycles are excluded from the analysis to eliminate acceleration and deceleration [86]. Baseline characteristics (see the ‘ Baseline factors’ section) are collected via a questionnaire filled out by the participants electronically in the eCRF or, in case not able to do so, on paper and transferred to the eCRF by the investigators. The results of FMA-LE, FAC, and BBS (see the ‘ Baseline factors’ section) are directly entered into the eCRF. ‘ Intervention and further activity outcomes’ are collected within the eCRF throughout the intervention (T0–T1) and follow-up (T1–T2) periods, respectively. In all phases, deviations from the protocol are recorded in the eCRF to ensure traceability and the ability to exactly repeat the assessment procedures at T0, T1, and T2 for each individual participant.

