### Frequency and plans for auditing trial conduct {23}

The project management group (including study staff from all sites) meets at least weekly to track correct trial conducted. As this is a low-risk study, no data monitoring committee exists; however, according to the approved study protocol by the cantonal ethical committee, an independent monitor performs at monitoring visits on the study documentation and procedures, including but not limited to the following actions:An initiation visit before the study start, where is evaluated whether ethical approval is granted, training of study staff was performed and documented, study and safety documentation as well as case report forms were appropriately prepared, and insurance is valid;At least one routine monitoring visit (further visits are planned if indicated due to inconveniences), where it is checked whether protocol and study documentation is up-to-date, informed consent procedures and enrolment are correctly performed, source data is correctly filed and data transferred to case report forms, safety is correctly reported and treated, and blinding has been maintained; andA closure visit upon the end of the study, where the monitor repeats the checks from the routine monitoring visit, and additionally assesses whether documentation is complete and archiving appropriately prepared.

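### At T1 and T2 an allocation-aware training supervisor accompanies the blinded assessor, an avoidable route for cues during the assessor-administered MoCA

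*Protocol article*

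**What the plan says.** Under Trial design {8} the article states: "The trial employs a single-blinded approach, with outcome assessors being unaware of group assignments". Under Who will be blinded {17a} it gives the means of protecting assessors: "They cannot access the randomisation tool in REDCap and are not involved in intervention procedures".

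Under Procedure for unblinding if needed {17b} it marks the item as not applicable, because assessors "are always accompanied by a training supervisor, who knows the participants and their group allocation". If allocation has to be known during a session, "the training supervisor can handle it and the assessor does not need to be unblinded".

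The primary outcome is described under Plans for assessment and collection of outcomes {18a}: "The MoCA (primary outcome) is executed on paper following the instructions of the providers". Assessors hold a MoCA certificate. Oversight of blinding is described under Frequency and plans for auditing trial conduct {23}: at one or more routine visits an independent monitor checks that "safety is correctly reported and treated, and blinding has been maintained", and at closure "the monitor repeats the checks from the routine monitoring visit".

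**The concern.** Participants know whether they trained, and supervisors know who trained. Protection against expectation in the person giving and scoring the MoCA therefore depends heavily on that person not learning the arm. The accompanying person's relationship with the participant differs systematically by arm. A greeting, a shared reference to a game or visible ease between the two can suggest the allocation without anyone breaking a rule.

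If an assessor does form a belief about the arm, any leniency in prompting or scoring would most plausibly favour the intervention, and it would fall on the primary outcome. With no participant-level record of what assessors believed, the trial report would have little to set against that suspicion.

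**Working it through.** The plan gives no figure on this point and no calculation can settle it. The check is to set the sections side by side.

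1. **Which visits are exposed.** Participant timeline {13} places the baseline measurement before random allocation, so nobody knows the arm at T0. Table 2 agrees: it lists an assessor at T0 and a blinded assessor at T1 and T2. The exposure is two visits per participant, or 38 × 2 = 76 visits for the target sample with complete follow-up.

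2. **Who is with the assessor.** Section {17b} says always a training supervisor who knows both the participant and the allocation. This is a stated procedure, given as the reason why no unblinding procedure is needed. It is not a detail lost when the protocol was condensed into an article.

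3. **How contact differs by arm before T1.**
   - Intervention arm: 2 sessions per week × 12 weeks = 24 planned sessions ({11a}), all supervised one-to-one ({11c}).
   - Control arm: no additional intervention and one call per week ({6b}), so about 12 calls over the same 12 weeks.
   - Both arms are interviewed weekly about activities up to T2, and Table 2 names the training supervisor as staff for both periods.
   - The article does not say whether the supervisor attending a visit is the one who trained that participant.

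4. **What the stated safeguards cover.** Hiding the randomisation instrument ({16a–c}, {17a}) and keeping assessors out of the training ({17a}) close off records and direct involvement. Neither addresses what an assessor may notice in the room. The double check of data entry under Data management {19} verifies the values entered; it is not described as a second scoring of the MoCA.

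5. **Whether the stated purpose needs the supervisor in the room.** The purpose in {17b} is that someone who knows the allocation can step in. A supervisor on call nearby meets that purpose during a seated test. The one assessment for which the article itself requires two investigators is the outdoor walk (Secondary outcomes), not the MoCA.

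6. **What evidence on blinding will exist.** The monitor checks blinding at one or more routine visits and again at closure ({23}). Deviations from the protocol are recorded in the eCRF ({18a}) and reviewed by the monitor ({21a}), so an overt disclosure could be captured. A familiarity cue would not register as a deviation, because the supervisor's attendance is itself the procedure. No item for the assessor's guess of the arm, and no dedicated item for unblinding, is described.

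**The case against.** A fair defence has several parts.

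- **The blind is not shown to be broken.** One might infer from {17b} that assessors in practice learn the arm. The article does not support that. It says supervisors know the participants without limiting this to one arm, and controls also have weekly contact. This stands: only a route for cues is shown.
- **Blinding is checked.** A reader might infer that nobody verifies it. Section {23} says otherwise, and recorded deviations add to it. This stands. What remains is narrower: no participant-level record is described.
- **Baseline is not exposed.** The word always in {17b} might suggest that every measurement is affected. Randomisation follows T0, so this reading fails.
- **Other protections exist.** Assessors are certified and follow the test provider's instructions, the computer tests and gait sensors produce automated output, and a de-identified dataset is planned to blind the analyst. It would be wrong to call assessor blinding the sole guard against measurement bias. None of these, however, removes a cue while the MoCA is being administered.
- **Conduct rules may sit in the full protocol.** Seating and rules on conversation are commonly left out of an article, so their absence here is not a fault. The point rests instead on what {17b} affirmatively fixes.
- **It is late.** At submission 37 participants had completed or were due to complete, against a target of 38, with completion expected by July 2024. This stands and limits the benefit.

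**Conclusion.** The point holds as an avoidable design weakness at T1 and T2, worth correcting because the remedy is cheap and the outcome concerned is the primary one. It is not an error of calculation and not a demonstrated failure of blinding.

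Its size is unknown. Nothing in the article allows a shift in MoCA score to be estimated, and any figure would be arbitrary. The direction, in favour of the intervention, is a judgement about how expectation usually acts.

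The conclusion rests on two assumptions: that accompanying the assessor means being within sight or hearing during the MoCA, and that in-person training creates more recognisable familiarity than weekly calls do. If the full protocol already keeps the supervisor outside during seated tests, {17b} needs only to be reworded to say so.

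**What to change.** Amend {17b} so that at T1 and T2 the training supervisor stays on call outside the room during the MoCA and the other seated cognitive tests. The supervisor attends only where needed, for example at walking tests, and does not discuss training there. Someone who knows the allocation remains available, as the section intends.

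For the remaining T1 and T2 visits, add an eCRF item completed by the assessor right after the visit, recording any unblinding and a guess of the arm. Report both by arm, with the number of visits at which they were collected. The trial report should also state how earlier visits were attended.

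The cost is a procedure note and one eCRF item, with no extra staff. The limitation is coverage: visits already held cannot be repaired, the article does not say how many remain, and the resulting record will be partial and should be described as such.

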## Data collection and management

### Plans for assessment and collection of outcomes {18a}

All outcome variables are gathered in an eCRF (see the ‘Data management’ section). All study-team members gathering data receive specific training for the relevant study procedures. Primary and secondary outcomes are collected at baseline (T0), post-intervention (T1), and follow-up (T2) measurements. The MoCA (primary outcome) is executed on paper following the instructions of the providers (mocacognition.com [93]), and the data is transferred into the eCRF. All assessors obtain a MoCA certificate (mocacognition.com) for trained execution of the test before performing the assessment in the study. The SIS 3.0 is collected via an online questionnaire filled out by the participants electronically in the eCRF or, in case not able to do so, on paper and transferred to the eCRF by the investigators. Secondary computer-based cognitive assessments are conducted within the Vienna Test System (VTS, Schuhfried GmbH, Mödling, Austria), a valid and reliable software for neuropsychological testing. All assessments include written instructions and practice sets and are only started if the participant received clarifying responses on any questions regarding the test functionality. The tests are performed on a touch-screen computer, using either one button on the keyboard or the touch screen to answer the stimuli. All cognitive outcome variables are obtained from the VTS result sheets and transferred into the eCRF. Outcome variables for the TUG and TUG-Cog are collected using a stopwatch and by noting correct answers on paper and directly entered into the eCRF. For the TUG, TUG-Cog, and the 10MWT, practice trials are performed before the actual assessment to ensure clarity of the procedure. Outcome variables of the gait assessments are gathered using the Gait Up system (Gait Up SA, Lausanne, Switzerland) with Physilog® sensors (wearable standalone movement inertial sensors, 50 × 37 × 9.2 mm, 19 g). The Gait Up system provides quantitative, objective, and valid assessment of gait movement [143] presented on output sheets, from where the data are transferred into the eCRF. The first and last two gait cycles are excluded from the analysis to eliminate acceleration and deceleration [86]. Baseline characteristics (see the ‘ Baseline factors’ section) are collected via a questionnaire filled out by the participants electronically in the eCRF or, in case not able to do so, on paper and transferred to the eCRF by the investigators. The results of FMA-LE, FAC, and BBS (see the ‘ Baseline factors’ section) are directly entered into the eCRF. ‘ Intervention and further activity outcomes’ are collected within the eCRF throughout the intervention (T0–T1) and follow-up (T1–T2) periods, respectively. In all phases, deviations from the protocol are recorded in the eCRF to ensure traceability and the ability to exactly repeat the assessment procedures at T0, T1, and T2 for each individual participant.

### Plans to promote participant retention and complete follow-up {18b}

During the follow-up period, participants in both groups are contacted once a week to inquire their usual care, general physical, and cognitive activities (see ‘Intervention and activity outcomes’). This keeps them engaged in the study procedures and, therefore, promotes successful retention.

### Data management {19}

An electronic case report form (eCRF) is kept for each enrolled participant using REDCap electronic data capture tools hosted at ETH Zurich [141, 142]. REDCap (Research Electronic Data Capture) is a secure, web-based software platform designed to support data capture for research studies, providing (1) an intuitive interface for validated data capture, (2) audit trails for tracking data manipulation and export procedures, (3) automated export procedures for seamless data downloads to common statistical packages, and (4) procedures for data integration and interoperability with external sources [141, 142]. This eCRF has been validated before enrolment of the first participant. Study team members who are authorised to enter or edit data in the eCRFs, receive a login to the REDCap study platform, and are listed with signatures in the trial master file (TMF) and the investigator site file (ISF). To assure that any authorised person, who may perform data entries and changes in the eCRF, can be identified, all entries/edits are recorded with name, date, and time. Data entry of the primary and secondary outcomes in REDCap is performed by one and double-checked by another investigator (verification, four-eyes-principle). Should any previously entered data need to be changed (e.g. because a mistake was identified during the verification), a reason must be given to proceed. eCRFs are kept current to reflect participant status at each phase during the study.

Study and participant data will be handled with uttermost discretion and are only accessible to authorised personnel who require the data to fulfil their duties within the scope of the study. Participants are coded and not identifiable in the eCRF or on any other study-specific documents. Appropriate coded identification (study ID) is used. Each study ID composes of four random letters or numbers, which are not related to any characteristics, or the time point of inclusion of the participants. The sponsor will store the participant identification list in a secured and locked location. All study data are archived for ten years after study termination or premature termination of the study.

### Confidentiality {27}

Personal information of potential and enrolled participants is kept confidential and only accessible for involved study-team members for study-related purpose. Data protection is kept according to current guidelines of the Swiss law. Participants, who have withdrawn from the study, can ask the deletion of their personal information at any time. All participants receive a study ID (a random sequence of four letters and numbers) not associable with their personal data. All study data is stored only with this ID and never related to any personal data. The key to decode study data is kept locked and only accessible for involved study-team members for study-related purpose(s). After completion of the study procedures, study data are archived according to Good Clinical Practice (GCP) guidelines for at least 10 years.

### Plans for collection, laboratory evaluation, and storage of biological specimens for genetic or molecular analysis in the trial/future use {33}

N/A as no biological specimens are collected in this study.

## Statistical methods

Microsoft Excel (Microsoft Corporation, 2016) will be used to aggregate and tabulate the data. All statistical analyses will be performed using RStudio open-source software (Bosten, USA [144]) or SPSS Statistics (version 26 for windows; IBM, Chicago, IL, USA).

### Statistical methods for primary and secondary outcomes {20a}

Distributions of all baseline factors and primary and secondary outcome variables will be checked with the Shapiro–Wilk test [145]. Appropriate descriptive statistics will be obtained for all baseline factors and outcome variables (means and standard deviations for normally distributed data, medians and inter-quartile ranges for non-normally distributed data, frequencies for categorical data). Differences between groups in baseline factors will be evaluated using an independent *t*-test if assumptions for parametric testing are met or a non-parametric alternative otherwise. For categorical data, a chi-square test or a Fisher’s exact test will be used as appropriate [146].

Assumptions on the residuals of primary and secondary outcomes will be checked using the DHARMa package in R [147]. Appropriate actions will be taken if one or more assumptions are not met. All primary and secondary outcomes will be analysed following the standard intention-to-treat (ITT [148, 149]) principle using linear mixed-effects models (LMEM, lme4 package in R). Subject-specific random intercepts will account for within-subject correlations between time points. Follow-up scores (T2) of the outcomes will be the dependent variables of the models, while group (intervention vs. control, control being the reference), time (T0, T1, T2), and group x time interactions at T1 and at T2, respectively, will be included as independent variables (fixed effects). Baseline factors such as age, sex, and time since stroke will be considered as covariates. Missing data of whole measurement time points (i.e. of dropouts) will be accounted for with the ‘last observation carried forward’ method. For single missing data points (e.g. if a participant did not perform an assessment at one time point or a technical issue produced missing data at one time point), however, no data imputation will be performed as LMEMs can be fitted even if some outcome data are missing [145, 150]. For the outdoor walking assessment (OWA), high occurrence of missing data is expected, as ability to walk 400 m is not covered by the eligibility criteria and varying weather conditions on the measurement days may interfere with the assessment. Therefore, for the OWA outcome parameters, datasets of participants who did not perform the OWA at one or several time points will be excluded from the analysis. Significance will be set to *p* < 0.05. Effect sizes will be calculated as *r* (Bravais-Person correlation coefficient) and interpreted as small (*r* < 0.3), medium (*r* < 0.5), and large (*r* ≥ 0.5) [145].

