## Outcomes {12}

Primary and secondary outcomes are collected at three time points (T0–week 0, T1–week 12, T2–week 24; see Table 2, Figs. 1 and 3) by cognitive and motor assessments as well as a health-related-quality-of-life questionnaire. At the baseline measurement (T0), participant characteristics and baseline factors are recorded. Intervention and activity outcomes are collected during the intervention (T0–T1) and the follow-up (T1–T2) periods, respectively. All variables will be aggregated as means or medians, depending on the distribution of the data, and the analysis metric for all will be final values (see the ‘ Statistical methods’ section). An overview of all outcome variables is presented in Tables 3 and 4.

**Table 2 Tab2:** Overview over outcome recording. *ADH*, adherence; *BBS*, Berg Balance Scale; *BQ*, baseline questionnaire, incl. see the ‘ Baseline factors’ section; *TUG(-Cogn)*, (cognitive dual-task) Timed Up and Go test; *CPL*, compliance; *FAC*, Functional Ambulation Category; *FM-LE*, lower-extremity component of Fugl-Meyer assessment; *MoCA*, Montreal Cognitive Assessment; *mRS*, modified Rankin scale; *MRT*, mental rotation test; *NBT*, N-back test; *NIHSS*, National Institute of Health Stroke Scale; *OWA*, outdoor walking assessment; *PCA*, physical and cognitive activities; *PP*, perceived performance; *PTD*, perceived task difficulty; *SIS 3.0*, Stroke Impact Scale; *SRT*, simple reaction test; *Stroop*, Stroop Interference test; *TMT*, Trail Making test; *UC*, usual care; *10MWT*, 10-m walk test

Time (weeks)	0	+ 1–12	+ 12	+ 13–24	+ 24
**Time point**	Baseline (T0)	Intervention period	Post-intervention (T1)	Follow-up period	Follow-up (T2)
**Study staff**	Assessor	Training supervisor	Blinded assessor	Training supervisor	Blinded assessor
**Baseline factors:** BQ, NIHSS, FAC, mRS, BBS, FM-LE	+				
**1° Endpoint:** MoCA	+		+		+
**2° Endpoints:** SIS 3.0, SRT, TMT, Stroop, NBT, MRT, TUG(-Cogn), 10MWT, OWA	+		+		+
**Intervention Endpoints:** CPL, ADH, PTD, PP		+ *(intervention group only)*			
**Activity Endpoints:** UC, PCA		+		+

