## Sample size {14}

A sample size of 38 participants (approx. 19 per group) was estimated for this study. The sample size estimation was based on systematic reviews investigating the effects of motor-cognitive training and exergames on cognitive functions. Stanmore et al. included studies with any population (including five out of seventeen studies with stroke or other neurological patients) and found a small to medium effect for global cognitive functioning (SMD = 0.44, *p* = 0.001) and several small to large effects for cognitive domains including executive functions, processing speed and visuospatial skills (0.26 ≤ SMD ≤ 0.90, *p* < 0.05) (132). Five further reviews included studies with older adults and found small to large effect sizes for global or overall cognitive functioning and cognitive domains including attention, executive functions, learning and memory, and processing speed (0.30 ≤ SMD ≤ 1.37, *p* < 0.05) [31, 35, 54, 56, 134]. Based on this evidence, a small to medium effect on global cognitive functioning is anticipated for the planned study (*f* = 0.21). The sample size was estimated using G*Power, entering this effect size (requiring no expected difference between groups and standard deviations) and the following parameters into the mask for a two-way mixed ANOVA; α-level = 0.05, power = 0.80, number of groups = 2, number of measurements = 3, correlation among rep measures = 0.5, nonsphericity correction = 1. Dropouts will be replaced by post-recruitment until the planned sample size is achieved. Based on the recent feasibility study [85] and comparable literature [135–137], a dropout rate of 10–20% can be expected.

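### The random-intercept-only model gives the T1 and T2 treatment terms one shared standard error, so the T2 test is too liberal if correlation fades with time; an unstructured covariance avoids this at little cost

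*Protocol article*

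**What the plan says.** Under the outcomes heading, "Primary and secondary outcomes are collected at three time points", namely "T0–week 0, T1–week 12, T2–week 24". The T0-T2 gap is therefore twice the T0-T1 gap.

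The section on methods for primary and secondary outcomes analyses all of them "using linear mixed-effects models (LMEM, lme4 package in R"). The treatment terms are the "group x time interactions at T1 and at T2, respectively, will be included as independent variables (fixed effects"). Dependence within a participant is handled by one device: "Subject-specific random intercepts will account for within-subject correlations between time points". The article states no random slope, no unstructured or autoregressive covariance and no robust standard error. It does promise a check of residual assumptions with DHARMa and suitable action if one fails. It names neither a check of the correlation pattern nor a fallback covariance.

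The sample size section makes the same equal-correlation assumption: "number of groups = 2, number of measurements = 3", one correlation of 0.5 for all pairs, and a nonsphericity correction of 1.

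One reading note: the methods section calls the T2 scores the dependent variable, yet time enters with three levels. I read the model as fitted to all three visits in long format, the only form in which its interaction terms can be estimated.

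**The concern.** A random intercept implies one variance at every visit and one correlation for every pair of visits. Scores 24 weeks apart are taken to be as alike as scores 12 weeks apart. With complete data, the T1 and T2 interaction terms then share a standard error built from the average of the three correlations.

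If the true correlations differ, at least one of those standard errors is wrong. The end-of-training contrast (T1) carries the primary objective. The T2 contrast carries the persistence question, which is secondary and exploratory. A significant group effect at either visit also triggers the clinical-meaningfulness and responder analyses, so excess false positives at T2 would pass into those. The same model serves every secondary outcome as well as the MoCA.

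**Working it through.** **1. The plan's own figure.** Inputs from the sample size section: "a small to medium effect on global cognitive functioning is anticipated for the planned study (*f* = 0.21"), "α-level = 0.05, power = 0.80", 2 groups, 3 measurements, correlation 0.5, nonsphericity correction 1. For the within-between interaction, λ = N·f²·m/(1−ρ) = 38 × 0.0441 × 3 / 0.5 = 10.05, with 2 and 72 degrees of freedom. Power is 0.8003, so 38 reproduces.

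**2. The standard errors.** Let r01, r12 and r02 be the correlations for T0-T1, T1-T2 and T0-T2, with equal variances (SD 1) and n = 19 per arm.

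- True variance of the group difference in change from baseline at visit j: 4(1 − r0j)/n.
- Variance the random-intercept model reports at both visits: 4(1 − r̄)/n on average, with r̄ = (r01 + r12 + r02)/3.
- Ratio of model SE to true SE: √[(1 − r̄)/(1 − r0j)].

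T2 is too narrow when r02 < r̄. T1 is too wide when r01 > r̄, that is when 2·r01 > r12 + r02.

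**3. One case in full.** Assume 0.8, 0.8, 0.64. Then r̄ = 2.24/3 = 0.747.

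- T1 ratio: √(0.253/0.200) = 1.125.
- T2 ratio: √(0.253/0.360) = 0.839.

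A single mixed-model fit to data simulated with correlations 0.7, 0.7, 0.49 confirmed the shared standard error: 0.236 for both interaction terms.

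**4. False-positive rates.** Simulations of 40,000 to 100,000 complete trials, 19 per arm, two-sided 0.05. The random-intercept test uses the pooled within-subject mean square on 72 df. All fading patterns are assumptions; the documents give only 0.5.

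| r01 / r12 / r02 | SE ratio T1 | SE ratio T2 | False positives T1 | False positives T2 |
|---|---|---|---|---|
| 0.5 / 0.5 / 0.5 (plan) | 1.00 | 1.00 | 4.9% | 5.0% |
| 0.5 / 0.5 / 0.45 | 1.02 | 0.97 | 4.7% | 5.6% |
| 0.7 / 0.7 / 0.65 | 1.03 | 0.95 | 4.3% | 6.2% |
| 0.5 / 0.5 / 0.4 | 1.03 | 0.94 | 4.3% | 6.4% |
| 0.75 / 0.75 / 0.65 | 1.06 | 0.90 | 3.7% | 7.6% |
| 0.6 / 0.6 / 0.36 | 1.10 | 0.87 | 3.3% | 8.8% |
| 0.8 / 0.8 / 0.64 | 1.13 | 0.84 | 2.9% | 9.8% |
| 0.8 / 0.8 / 0.6 | 1.15 | 0.82 | 2.5% | 10.8% |

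The same absolute fade does more damage at a higher correlation: a drop of 0.10 gives 6.4% from 0.5 and 7.6% from 0.75.

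**5. Patterns where r12 exceeds r01.** With 0.6 / 0.75 / 0.55, r̄ = 0.633. The T1 ratio is √(0.367/0.400) = 0.96, and T1 false positives are 6.1%. With 0.7 / 0.8 / 0.65 they are 5.5%. T2 stays too narrow in both (ratio about 0.90).

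**6. Carried-forward values.** With 10-20% dropout filled by last observation carried forward, and first-order autoregressive correlation of 0.5 to 0.7, the ratios are 1.03-1.11 at T1 and 0.85-0.88 at T2. The direction does not change.

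**7. The alternative.** With complete data, an unstructured covariance amounts to a visit-specific change-score test on 36 df. It held about 5% at both visits in all patterns tried. T1 power at a true effect of 0.44 SD:

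| Correlations | Random intercept | Unstructured |
|---|---|---|
| 0.8 / 0.8 / 0.64 | 46% | 55% |
| 0.5 / 0.5 / 0.4 | 25.2% | 26.6% |
| 0.5 throughout | 26.7% | 26.0% |

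With 0.5 throughout and an effect of 0.89 SD, power goes from 77.1% to 75.9%.

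**The case against.** The best defence is that nothing in the article is inconsistent. The sample size assumes one correlation of 0.5 and sphericity, and the random-intercept model is the analysis that matches; under that assumption both tests hold 5%. Participants are at least six months past their stroke and are followed for 24 weeks, so nearly stable correlation is plausible. The inflation falls on a secondary contrast. Residual checks are promised, and fallback covariance structures are often left to an analysis plan that is not shown.

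Much of this stands. No correlation by lag is documented, so no error is demonstrated, only exposure to one. What does not stand is the safeguard: the residual check names no look at the correlation pattern and no alternative, and a covariance chosen after seeing the data would be post hoc. The random intercept is also not left open; the article specifies it.

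A reader might go further and conclude that T1 intervals are too wide and the primary contrast loses power. The documents do not support that as a general statement. It requires 2·r01 > r12 + r02. Training takes place only between T0 and T1, so if response varies between people, r12 may exceed r01, and the T1 test then becomes slightly liberal. The 46% versus 55% power comparison likewise belongs to one strong-fade pattern; under 0.5 / 0.5 / 0.4 the gain is about 1 point.

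**Conclusion.** The point holds conditionally. The specified model ties the T1 and T2 treatment terms to one standard error, which is right only if correlation and variance are constant over the 24 weeks. Over the patterns tried in which correlation fades equally per 12-week step, T2 false positives run from 5% (no fade) through about 6% (mild fade) to about 11% (0.8 falling to 0.6). T1 runs from about 2.5% to 5% in those patterns, and reaches about 6% where the T1-T2 correlation clearly exceeds T0-T1.

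These figures rest on assumed correlations, equal variances, complete data and 19 per arm. The effect of unequal variances was not computed. It would also be wrong to infer that 38 is miscalculated: it reproduces under its stated inputs. This is a cheap improvement in robustness, not a demonstrated error.

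**What to change.** Keep the fixed effects. Pre-specify, before outcome data are analysed by group, an unstructured 3 x 3 within-subject covariance with Kenward-Roger or Satterthwaite degrees of freedom (for example with the mmrm package in R instead of lme4). State that the random-intercept model is used only if that fit does not converge, and report where this happens.

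The cost is a different model call and four more covariance parameters (six instead of two). If equal correlation is true, the loss is about 1 percentage point of power or less. That figure comes from complete data; the unstructured fit was not tested with dropout, carried-forward values or covariates. Some secondary outcomes may fail to converge, which is why the fallback should be written down. Data collection and sample size are unaffected.
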